## Methods and analysis

The study is a two-arm trial involving 300 patients (*n* = 150 in the VAE group and *n* = 150 in the non-VAE group) over 36 months. Participants are randomly assigned to either the VAE (intervention) or standard-of-care (control) group.

In the control group, biopsies will follow the typical sampling procedure aimed only at collecting some microcalcifications from the target. In the VAE group, the focus will be on the complete removal of the biopsy target, confirmed by mammography on the biopsy table, followed by a second sequence of cleaning samples. Radiograms will confirm lesion removal for the intervention group. Pathology analysis will report separately each sample. Pathological outcomes at surgery will be compared between the two groups. To adhere to the protocol, it is necessary to have a digital stereotactic biopsy guidance system (with a dedicated patient table).

A statistical comparison will be performed to evaluate the differences between the VAE and Standard-of-care groups.

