### Study design

All patients with suspicious breast lesions (BI-RADS ≥3) who are candidates for stereotactic VABB and whose lesions present as microcalcifications (the most common form of low and intermediate-grade DCIS) will be prospectively selected. The radiologists involved in the procedure are all dedicated to breast imaging and have at least 5 years of work experience. Patients with a mammographic lesion measuring less than 15 mm in diameter will be enrolled and randomly assigned into two groups on a 1:1 basis. The randomization data will be securely stored on a password-protected computer at the European Institute of Oncology, accessible only to researchers involved in the study.

In the control group, biopsies will focus solely on sampling a few microcalcifications (fewer than 12 samples) and may not necessarily use an 8G needle. In the VAE group, the lesion will be macroscopically removed using an initial sequence of at least eight samples with an 8G needle, followed by a cleaning sequence of at least four samples. This group will undergo an excisional biopsy (VAE) according to United Kingdom guidelines, which define VAE as a collection of at least 4 grams of tissue with an 8G needle. The VAE will be performed during the same biopsy session without recalling the patient later. Both groups will receive post-procedure mammograms and specimen radiograms. The specimen radiogram is used to separate the specimens with microcalcifications from those without, to assist the pathologist, and to verify that the biopsy procedure has indeed sampled the target microcalcifications. We also have the ability to obtain mammographic images while the patient is still on the biopsy table. For the interventional group, if residual microcalcifications are present, the sampling will continue until they are completely removed. For the control group, the goal is not the complete removal of the target but rather the correct diagnostic procedure, so even if residual microcalcifications remain after the biopsy, the procedure will be concluded.

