#### Exclusion criteria

Patients undergoing other types of biopsies (not stereotactic).Patients whose lesions are not in the form of microcalcifications.Patients who refuse to sign the specific informed consent.Patients whose histological biopsy result is not low/intermediate-grade DCIS.Patients with multifocal and/or multicentric lesions.Patients who will not undergo surgery.For the VAE group only: patients in whom haematoma prevents the continuation of the second sequence of biopsies.

The data to be recorded during the biopsy procedure are listed in Table 1.

**Table 1 tab1:** Data recorded during the biopsy procedure.

Characteristics	
**Age (years)**	**Needle (Gouge)**
**Menopausal status**	7G
Pre-	8G
Post-	10G
**Lesion side**	11G
Right	**Samples (n)**
Left	**Lesion excision**
**Lesion site**	Minimal
Upper-outer	Partial
Lower-outer	Complete
Upper-inner	**Clip**
Lower-inner	Yes
Retroareolar	No
Inner-equatorial	**Clip placement**
Outer-equatorial	On-site
Upper-hemitelic	Dislocated
Lower-hemitelic	**Clip dislocation (from the sampling site)**
**Lesion size (mm)**	Distance (mm)
**Lesion type**	Sector (upper, lower, outer, inner)
Microcalcifications	**VAE**
Architectural distortion	Yes
Lump	No
Asymmetry	**Complications**
**VABB type**	Yes (additional notes)
Stereotactic	No
Tomographic	**Histological findings**
Ultrasound	

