### Statistical analysis

The primary endpoint is to compare the percentage of patients with no detectable pathology at surgery between the group undergoing standard treatment (macroscopical removal of the lesion) and the group undergoing VAE (VAE group). Based on the assumption that macroscopical removal without VAE will result in approximately 20% of patients having no pathology at the subsequent surgery, a sample size of 70 patients per arm is calculated to achieve 90% power to detect a 16% difference between the two treatment groups.

This calculation is based on an inequality test for two independent proportions, assuming a 0.2 proportion under the null hypothesis (standard treatment group) and a 0.04 proportion under the alternative hypothesis (VAE group). The test statistic will be the two-sided Z test with pooled variance, using a significance level 0.05.

Continuous variables will be summarized with the median and interquartile range for each treatment arm, while categorical variables will be presented as frequency and percentage. Differences between the two groups will be evaluated using the Wilcoxon rank-sum test for continuous variables and the chi-square test for categorical variables. Multivariate logistic regression models will be used to assess the association between the treatment group and the absence of pathology at surgery, adjusting for key clinical variables and potential confounders. The results will be quantified in terms of odds ratios (Ors), with statistical significance evaluated using *p*-values and a significance threshold set of 0.05.

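### The plan does not say whether the unadjusted Z test or the adjusted logistic model decides the primary endpoint, and lesion size, known before randomisation, is not tied to the primary test

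*Protocol article*

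**What the plan says.** The Statistical analysis section of the Protocol article makes the percentage of patients with no pathology at surgery the primary endpoint. It states that "a sample size of 70 patients per arm is calculated to achieve 90% power to detect a 16% difference", and then: "The test statistic will be the two-sided Z test with pooled variance, using a significance level 0.05". That test uses no covariate.

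The next paragraph names the chi-square test for categorical variables. It also plans multivariable logistic models relating treatment group to absence of pathology at surgery, adjusted for clinical factors and confounders that are not listed, with odds ratios and p-values judged at 0.05. The Methods part of the Abstract likewise mentions statistical tests and logistic models together, without ranking them.

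On lesion size, Study design says: "Patients with a mammographic lesion measuring less than 15 mm in diameter will be enrolled and randomly assigned into two groups on a 1:1 basis". Table 1, under Exclusion criteria, records lesion size in mm.

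**The concern.** Two analyses of one endpoint, each judged at 0.05, have no stated order. If one gives p below 0.05 and the other does not, the article does not say which answers the primary question.

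The only test tied to the primary comparison also ignores a baseline value that every patient has. Size plausibly bears on the outcome: a lesion of a few millimetres may be cleared even by limited sampling, while one near the limit may not. Study design itself caps size and asks whether VAE can remove small lesions. An unadjusted test leaves any size-related variation in the error and is exposed to chance imbalance in size between groups of about 70. Adjusting for a prognostic baseline value recovers some of that power without more patients or data.

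**Working it through.** **Inputs from the documents.** Two-sided alpha 0.05, pooled variance, 90% power, 70 per arm, rates 0.20 (control) and 0.04 (VAE), all from Statistical analysis; 1:1 allocation from Study design; 300 patients, 150 per arm, from Methods and analysis.

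**Input that is assumed.** The strength of the link between size and outcome. The documents give none, so a range is run.

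**Step 1: the plan's own figure.** n per arm = [1.960·√(2·p̄·q̄) + 1.282·√(p1q1 + p2q2)]² / (p1 − p2)².
- With 0.20 and 0.04, p̄ = 0.12. n = [1.960·√0.2112 + 1.282·√0.1984]² / 0.16² = (0.901 + 0.571)² / 0.0256, which gives 85 per arm, not 70.
- Power at 70 = Φ[(0.16·√70 − 0.901) / 0.445] = Φ(0.983) = 83.7%.
- Only a one-sided 0.05 test comes close to the stated figure (69 per arm), but the text says two-sided.

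**Step 2: the alternative in the direction of the hypothesis.** The 20% is the control rate of "approximately 20% of patients having no pathology at the subsequent surgery". If VAE clears more lesions, a 16-point gain means 36%. The same formula then gives 164 per arm, with power of 56% at 70 and 87% at 150. Both alternatives are carried forward.

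**Step 3: formula check on adjustment.** If size explains a share R² of the outcome variance, n acts like n/(1 − R²). With n = 70:

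| R² | 70/(1 − R²) | Power, 20% v 4% | Power, 20% v 36% |
|---|---|---|---|
| 0 | 70.0 | 83.7% | 56.0% |
| 0.02 | 71.4 | 84.5% | 56.8% |
| 0.05 | 73.7 | 85.6% | 58.2% |
| 0.10 | 77.8 | 87.4% | 60.5% |
| 0.20 | 87.5 | 91.0% | 65.7% |

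**Step 4: simulation.** 3,000 trials per setting, pooled Z test against a logistic score test for arm adjusted for one continuous covariate, with an assumed odds ratio (OR) per standard deviation (SD).

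| Rates | n per arm | OR 1.5 | OR 2 | OR 3 |
|---|---|---|---|---|
| 20% v 36% | 70 | 58.4 → 60.0 | 56.7 → 60.8 | 55.9 → 63.5 |
| 20% v 36% | 150 | 88.2 → 89.3 | 86.9 → 89.5 | 88.2 → 93.0 |
| 20% v 4% | 70 | 87.2 → 87.9 | 86.9 → 88.2 | 86.5 → 89.5 |
| 20% v 4% | 150 | 99.5 → 99.6 | 99.6 → 99.6 | 99.4 → 99.7 |

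Each cell is power in %, unadjusted → adjusted. Simulated unadjusted power at 20% v 4% is about 87%, against 83.7% by formula, because the normal approximation is rough at a 4% rate. Both are below 90%.

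**Step 5: the same on the mm scale.** If sizes spread evenly over 3–15 mm (assumed), the SD is 12/√12 = 3.46 mm. An OR of 0.5, 0.3 or 0.2 per 5 mm is then 0.62, 0.43 or 0.33 per SD, or inverted about 1.6, 2.3 and 3. Runs on this scale gave 55 → 57%, 59 → 64% and 57 → 66% for 20% v 36%, and 88 → 89%, 86 → 89% and 88 → 90% for 20% v 4%. This is close to Step 4.

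**Step 6: type I error.** With both arms at 20%, across covariate strengths and both sample sizes, rejection was 4.5–5.7% for the Z test and 4.2–5.7% for the adjusted score test. The Monte Carlo standard error is √(0.05·0.95/3000) = 0.4 points.

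**The case against.** **Adjustment is already planned.** A reader might infer that the plan forgoes adjustment and simply gives power away. The documents do not support that: Statistical analysis and the Abstract both plan adjusted logistic models on this endpoint. What remains is that the model is not tied to the primary decision and size is not named in it.

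**The Z-test sentence may only describe the sample-size calculation.** It does sit in that paragraph. But the analysis paragraph then offers the chi-square test, which without continuity correction is the square of the pooled Z. The comparison is unadjusted on either reading, and the order of the analyses is still open.

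**A covariate list can be left to the full protocol or SAP.** True, and its absence alone would be no finding. The point concerns what the article does fix: one unadjusted test for the primary comparison and an adjusted model beside it, with no statement of which decides.

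**The size effect is assumed and may be weak.** This stands. Over 3–15 mm, odds ratios of 0.3 and 0.2 per 5 mm mean 18-fold and 48-fold differences in odds (1/0.3^2.4 and 1/0.2^2.4). In the VAE arm, sampling continues until no calcifications remain, which may flatten any size effect there. The upper end of the gain should be read as a ceiling.

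**The analysed number may be larger.** Methods and analysis says "The study is a two-arm trial involving 300 patients". At 150 evaluable per arm the gain at 20% v 4% is under half a point. But patients without low- or intermediate-grade DCIS on biopsy are excluded after the procedure, so 150 evaluable is not assured.

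**An unadjusted test is valid under randomisation.** Also true. The choice costs some precision; it is not an error of validity.

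**Conclusion.** The point holds in a limited form. The article names an unadjusted test for the primary comparison, plans an adjusted model on the same endpoint at the same level, and does not say which decides. Lesion size is available before randomisation and is not tied to the primary test.

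The gain from adjusting at 70 per arm is about 1 to 2 points of power if size is a weak predictor and up to about 8 if it is strong, for 20% v 36%. It is smaller for 20% v 4%: about 1 to 3 points in the runs shown, and no more than about 5 in others. Adjustment by a real predictor did not lose power in these runs, and type I error stayed near 5%. All of this rests on the assumed size effect.

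A reader might also infer that a sample size based on the Z test becomes conservative once the analysis is adjusted. It does not. At the stated rates 70 per arm gives about 84% by formula, and at 20% v 36% even the strong-effect case reaches only about 64% in the Step 4 table. Adjustment also does not repair the exclusions made after randomisation.

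**What to change.** In Statistical analysis:
- Make the primary analysis a single logistic model with arm and pre-biopsy mammographic lesion size (continuous, in mm) as its only terms, and state that its arm effect decides. Specify the size used for eligibility, since Table 1 is a record made at the biopsy procedure.
- Report the standardised (g-computed) difference in the percentage with no pathology beside the odds ratio. The endpoint is framed as a difference in percentages, and a conditional odds ratio alone is a different measure.
- Keep the two-sided pooled Z test as the unadjusted sensitivity analysis, and label other adjusted models as supportive.
- Do not describe the sample size as conservative. Correct it separately: the 90% power claim, the 0.04 rate that runs against the endpoint's direction, and the gap between 70 and 150 per arm.

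The cost of the analysis change is a few sentences, with no new data or patients. The small downside is that the deciding p-value no longer comes straight from the raw 2×2 table, so the unadjusted result should be shown next to it.

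### At 70 per arm and the stated rates, the adjusted odds ratio rests on about 17 rarer-outcome patients: about 6% of trials give no finite maximum-likelihood value, and the rest carry a modest average bias away from 1

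*Protocol article*

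**What the plan says.** All of this is in the protocol article, section Statistical analysis.

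- Size: "a sample size of 70 patients per arm is calculated to achieve 90% power to detect a 16% difference between the two treatment groups".
- Rates: "assuming a 0.2 proportion under the null hypothesis (standard treatment group) and a 0.04 proportion under the alternative hypothesis (VAE group"). The 20% is tied in words to "approximately 20% of patients having no pathology at the subsequent surgery" in the control arm.
- Primary test: "The test statistic will be the two-sided Z test with pooled variance, using a significance level 0.05".
- Adjusted analysis: "Multivariate logistic regression models will be used to assess the association between the treatment group and the absence of pathology at surgery", with adjustment for clinical variables and confounders that are not named or counted.
- Reporting: "The results will be quantified in terms of odds ratios (Ors), with statistical significance evaluated using" p-values against a 0.05 threshold.

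The section names no penalised or exact estimation method. Elsewhere the article gives another size: Methods and analysis plans 300 patients, 150 per arm, and Study design aims for at least 300.

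**The concern.** A logistic model's stability depends on how many patients have the rarer outcome and how they split between the arms, more than on the total enrolled. At the stated rates and size, the VAE arm is expected to hold about three such patients. If it holds none, the maximum-likelihood odds ratio runs off to zero or infinity, with or without covariates. If it holds one or two, an estimate exists but is imprecise, and each added covariate pushes it further from 1 on average.

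The odds ratio is how the plan intends to express the VAE effect after adjustment. At stake is whether that figure will exist, and whether its size reflects VAE or sparse data.

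**Working it through.** **Inputs.** From Statistical analysis: 70 per arm, rates 0.20 and 0.04, two-sided alpha 0.05, pooled Z test, 90% power. From Methods and analysis: the alternative size of 150 per arm. Number and strength of covariates: not given, so assumed.

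**1. The plan's own figure.** The pooled-variance formula is n = [z(α)·√(2·p̄·(1−p̄)) + z(β)·√(p₁(1−p₁) + p₂(1−p₂))]² / (p₁−p₂)², with p̄ = 0.12.

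- Two-sided: [1.960·√0.2112 + 1.282·√0.1984]² / 0.16² = 85 per arm. The power at 70 is 83.7%.
- One-sided alpha 0.05: 69 per arm.

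So 70 does not follow from the two-sided test as stated. That is a separate matter, and the stated 70 is used below.

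**2. Rarer-outcome counts.** 70 × 0.20 + 70 × 0.04 = 14 + 2.8 = 16.8. The count is the same if both figures are rates of remaining pathology.

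**3. Empty VAE cell.**

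- P(0 of 70) = 0.96⁷⁰ = 5.7%.
- P(0 or 1) = 0.0574 + 70 × 0.04 × 0.96⁶⁹ = 22.5%.

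With 14/70 against 0/70 there is no finite odds ratio, yet the pooled Z is 0.20 / √(0.1 × 0.9 × 2/70) = 3.94.

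**4. Behaviour of the maximum-likelihood estimate at 70 per arm.** The unadjusted case was enumerated exactly. The others were simulated, 3,000 trials per setting, with half the covariates continuous and half binary (approximately). The strength is the assumed log odds ratio of each covariate.

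| Covariates (strength) | No finite OR | True log OR | Mean log OR where it exists | Too far from 0 by | Trials overstating |
|---|---|---|---|---|---|
| 0 | 5.7% | −1.792 | −1.844 | 3% | 51% |
| 3 (0) | 5.1% | −1.792 | −1.877 | 5% | 52% |
| 3 (0.5) | 5.9% | −1.920 | −2.034 | 6% | 54% |
| 5 (0) | 6.0% | −1.792 | −1.923 | 7% | 55% |
| 5 (0.4) | 5.9% | −1.929 | −2.116 | 10% | 56% |
| 8 (0.3) | 6.4% | −1.916 | −2.200 | 15% | 60% |

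The fifth column is mean/true − 1, for example 2.200/1.916 − 1 = 15%. With eight covariates of no prognostic value it is about 11%.

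**5. Sensitivity to the inputs.**

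- 150 per arm at 0.20 and 0.04: 30 + 6 = 36 patients with the rarer outcome, and P(0 of 150) = 0.96¹⁵⁰ = 0.2%. The mean log odds ratio is still about 4 to 8% too far from 0.
- 70 per arm at 0.20 and 0.36 (an assumption; 0.36 is not in the document): 14 + 25.2 = about 39 patients and practically no empty cell. With five covariates of strength 0.4, the odds ratio at the mean log is 2.74 against a true 2.53, a factor of 1.08. At 0.04 the same model gives 0.121 against 0.145, a factor of 1.20.

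**6. Firth's method at 70 per arm, 0.20 and 0.04.** The estimate is always finite. The mean log odds ratio is −1.76 to −1.80 against −1.79 (covariates without prognostic value), and −1.91 to −1.92 against −1.92 to −1.93 (prognostic covariates).

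**The case against.** Several objections have force.

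- **The primary test does not need the model.** True. The pooled Z test stays computable when the VAE cell is empty, so a reader who inferred that the primary comparison can fail would be wrong.
- **The odds ratio is not overstated in every trial where it exists.** True. A reader might infer that from the word bias, but the bias is an average. Between 40% and 49% of those trials understate the effect.
- **The analysed number is not settled.** True. Randomisation comes before histology is known, and only low- or intermediate-grade DCIS patients who have surgery are compared, so 300 may mean enrolment. But those conditions are also listed as inclusion criteria, so 300 may mean analysed patients. The 6% applies at 70 per arm, the only size the article justifies.
- **The 0.04 is itself doubtful.** True. As worded it is a lower no-pathology rate under VAE, against the trial's hypothesis. If both rates mean remaining pathology, nothing above changes. If the 20% keeps its label and only the 4% means remaining pathology, the rarer outcome totals 56 + 2.8 = 58.8. The 5.7% risk of an empty cell then persists, but the overall scarcity does not.
- **Maximum likelihood and Wald p-values are not named.** True. Maximum likelihood is inferred because no alternative is given, and a fuller document could specify one. It is tempting to add that the model's p-value would contradict the Z test when the VAE cell is empty. That holds for a Wald p-value, not for a likelihood-ratio one, and the article does not say which is meant.
- **The covariate numbers are invented.** True for every row with covariates. The 5.7% and the 3% need none.

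What stands is that the method as stated, at the rates and size as stated, has a known weakness with a cheap remedy.

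**Conclusion.** The point holds as a modest improvement to the adjusted analysis. With 70 analysed per arm and 0.20 and 0.04 as rates of the same outcome, the maximum-likelihood odds ratio has no finite value in about 6% of trials. In the others its average bias away from 1 on the log scale is about 3% unadjusted and grows with the number of covariates, to 11 to 15% at eight. The conclusion rests on four things: the 70 per arm, the shared label of the two rates, the reading of the model as maximum likelihood, and (for the larger bias figures only) assumed covariates. With 150 analysed per arm, or a VAE rate of 0.36, the risk of a non-finite estimate all but disappears and only some average bias remains.

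**What to change.** State in the Statistical analysis section that the adjusted odds ratio will be estimated by Firth penalised-likelihood logistic regression, with profile-likelihood confidence intervals and p-values. Fix a small number of covariates in advance, all measured before randomisation. State that Table 1 items arising from the biopsy procedure, such as needle gauge, number of samples and extent of lesion excision, will not be used: they follow randomisation and partly define the arm. The article does not say they would be used, but its open wording allows it.

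The cost is a few lines of text and a standard software routine. The downside is slight shrinkage of the odds ratio and fewer covariates. No extra patients or data are needed, and the primary Z test stays as it is.

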## Discussion

DCIS is currently treated aggressively due to the challenge of predicting which cases will progress to invasive BC (9). Standard treatment typically involves surgical excision, and patients opting for breast-conserving surgery often receive adjuvant local RT to reduce the risk of local recurrence (10). Additionally, adjuvant endocrine therapy May be recommended based on the tumour’s hormone-receptor status to minimize further the recurrence risk in patients undergoing breast conservation (11). Long-term survival rates for DCIS remain high regardless of the surgical approach or use of RT, with cause-specific survival rates of 98.9% at 10 years and 96.7% at 20 years (12).

There is growing interest in reducing the intensity of DCIS treatment due to several conditions. DCIS has a low BC-specific mortality rate, whether treated with standard methods or potentially even without treatment (13). A SEER study of 108.196 DCIS patients treated with standard methods reported BC-specific mortality rates of 1.1% at 10 years and 3.3% at 20 years (14). Autopsy studies have found undiagnosed DCIS in up to 39% of women who died from non-BC causes, indicating that DCIS can remain non-aggressive and May not always progress to significant disease in some women (15). Moreover, the widespread use of mammography has led to increased detection of DCIS, but this has not corresponded to a decreased incidence of invasive cancer, suggesting that DCIS may not always evolve into invasive carcinoma (16).

A major focus in reducing DCIS treatment is identifying women who might not require surgery after diagnosis. These patients could be managed with active surveillance, potentially with or without endocrine therapy. Four phase III prospective trials are exploring active image-based surveillance for patients with low-risk DCIS: COMET in the United States, LORD in Europe, LORETTA in Japan, and LORIS in the United Kingdom (17). The trials primarily aim to monitor the progression to ipsilateral invasive cancer. Due to low enrollment, the LORIS and LORD trials have transitioned to registry studies (18).

We propose that radiology can play a crucial role in reducing the diagnostic underestimation of biopsies and, through this study protocol, position itself as a viable alternative to surgery.

This approach can help identify patients for whom active surveillance is a safe option.

Our study aims to identify patients for whom active surveillance can be safely recommended, thereby increasing the enrollment in non-operative management of DCIS. The role of VAE as a potential alternative to surgery has already been successfully investigated for benign lesions and, in preliminary stages, for high-risk lesions (19). We believe that its role in managing *in situ* lesions could be equally promising.

One of the study’s strengths is the integration of VAE on the same day and during the same session as the conventional biopsy procedure. This method offers significant time and economic savings and reduces psychological stress for the patient. However, this protocol will likely result in performing VAE in many patients who do not have *in situ* pathology, as the histological outcome is not known at the time of the biopsy. We believe the risks associated with VAE are minimal and not significantly higher than those of the standard stereotactic procedure. Anyway, the percentage of hematomas and peri-biopsy complications will be recorded and compared between the two groups.

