All patients with low and intermediate-grade DCIS histological findings will be included in the study and are expected to be evenly distributed between the VAE and control groups. These patients will undergo surgery, and we will compare the percentage of patients with no pathology (including *in situ*) at the surgery between the two groups to determine if VAE can effectively remove small lesions and potentially serve as an alternative to surgery. The surgical specimens will be radiographed to verify the presence of the post-biopsy clip in the surgical sample. We will also compare the rate of biopsy underestimation of invasive carcinoma between the groups. The surgical tissue sections will be documented to ensure consistency between the two groups.

Our goal is to enroll at least 300 patients in this study. We focus on stereotactic VABB because *in situ* neoplasms predominantly present as microcalcifications, and complete macroscopic removal of the lesion can be more easily verified with mammography rather than ultrasound. The study design is summarized in Figure 1.

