#### Inclusion criteria

Patients with suspicious breast lesions (BI-RADS ≥3) presenting as microcalcifications.Patients capable of and willing to comply with the specific informed consent form.Patients undergoing stereotactic VABB.Patients with low to intermediate-grade DCIS following biopsy.Patients scheduled for surgery.

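### Read as written, the eligibility criteria drop from the complication comparison the patients without DCIS who receive VAE, and drop some haematomas from the VAE arm only

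*Protocol article*

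**What the plan says.** All references are to the protocol article.

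- **Order of events (Study design).** "Patients with a mammographic lesion measuring less than 15 mm in diameter will be enrolled and randomly assigned into two groups on a 1:1 basis". VAE follows in the same session, with no later recall, so both allocation and procedure precede histology.
- **Admitted exposure (Discussion).** "this protocol will likely result in performing VAE in many patients who do not have *in situ* pathology". The reason given is that the pathology result arrives only after the session.
- **The answer given (Discussion).** The authors believe the added risk is small, and add that "the percentage of hematomas and peri-biopsy complications will be recorded and compared between the two groups".
- **Who is in the study.** Study design: "All patients with low and intermediate-grade DCIS histological findings will be included in the study". Inclusion criteria: "Patients with low to intermediate-grade DCIS following biopsy", and surgery must be scheduled. Exclusion criteria: "Patients whose histological biopsy result is not low/intermediate-grade DCIS", and patients who will not have surgery.
- **One-arm exclusion (Exclusion criteria).** In the VAE group only, a patient is excluded if a haematoma prevents the second sequence of samples.
- **Data collected (Table 1).** The biopsy record includes complications, whether VAE was done, and histological findings.

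No section defines a separate safety population.

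**The concern.** The complication comparison is the only empirical check the article offers on a cost it acknowledges itself: the larger procedure is performed before anyone knows whether DCIS is present. Complications of the biopsy session occur in a randomised patient before the histology and surgery criteria can be applied. If those criteria nevertheless define who is counted, a patient with a benign result and a large haematoma after VAE is not in the comparison. Same-session VAE would in practice be applied to everyone biopsied for small microcalcifications, so that is the population in which its complication rate needs to be known.

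The one-arm haematoma exclusion adds a second problem. Haematoma is the named safety outcome, and some of the more consequential ones would be removed from the VAE arm with no matching removal from the control arm.

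**Working it through.** **1. Who would be counted, on the stated criteria.**

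| Randomised patient, biopsy done | In the study? | Criterion |
|---|---|---|
| Benign or other result without DCIS | No | histology |
| High-grade DCIS or invasive result | No | histology |
| Low/intermediate-grade DCIS, no surgery | No | surgery |
| VAE arm, haematoma stops second sequence | No | VAE-only exclusion |
| Control arm, haematoma | Yes, if DCIS and surgery criteria are met | none |
| Low/intermediate-grade DCIS, surgery | Yes | none |

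The patients named in the Discussion fall in the first row. The excluded set is wider than that row.

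**2. Direction of the one-arm exclusion.** Let p be the VAE-arm complication rate and h the part of it made up of haematomas that stop the second sequence. After exclusion the rate is (p − h)/(1 − h), which is below p whenever h > 0 and p < 1. The control rate is untouched, so the comparison shifts in favour of VAE. Each such event taken out lowers the VAE rate by about 1/70 = 1.4 points with 70 in the arm, or 1/150 = 0.7 points with 150.

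**3. How many are left out.** The article states no figure for the complication comparison, so there is none to reproduce. Inputs from the article: 150 per arm (Methods and analysis) and 70 per arm (Statistical analysis). The 70 is used here only as a possible denominator; whether it follows from its own inputs is a separate matter. Assumptions, not in the article: a yield y of qualifying DCIS of 20%, 30% or 47% (the last is simply 70/150, not an estimate), and a 5% complication rate in each arm.

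The share left out on histology is 1 − y: 80%, 70% or 53%. Absolute numbers depend on what the 300 counts. Half-width of the 95% interval for the difference = 1.96 × √(2 × 0.05 × 0.95 / n).

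*If the 300 are biopsied patients (150 per arm):*

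| y | counted = 150y | left out | half-width, counted | half-width, all 150 |
|---|---|---|---|---|
| 20% | 30 | 120 | 11.0 points | 4.9 points |
| 30% | 45 | 105 | 9.0 | 4.9 |
| 47% | 70 | 80 | 7.2 | 4.9 |

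*If the 300 are DCIS patients (150 per arm counted, half-width 4.9 points):*

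| y | biopsied = 150/y | left out | half-width, all biopsied |
|---|---|---|---|
| 20% | 750 | 600 | 2.2 points |
| 30% | 500 | 350 | 2.7 |
| 47% | 322 | 172 | 3.4 |

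Expected events at 5% are only 0.05 × 70 = 3.5 per arm with 70, and 1.5 with 30, so the normal approximation is rough at the small end.

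**4. Power for an assumed true difference.** For 5% against 10%, with a two-sided pooled Z test at 0.05, power is about Φ[(0.05 − 1.96 × √(2 × 0.075 × 0.925 / n)) / √((0.05 × 0.95 + 0.10 × 0.90) / n)]. At n = 70 this is Φ[(0.05 − 0.0873)/0.0443] = 20%. At n = 150 it is Φ[(0.05 − 0.0596)/0.0303] = 38%.

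**The case against.** The strongest reply is that the article never says these patients are omitted. It says only that the two groups will be compared, and Study design forms two groups at randomisation, before histology. The promise comes just after the remark about patients without in situ disease, so it can be read as covering them. Table 1 collects complications and histology as biopsy data. A condensed article may also leave the naming of a safety set to a fuller document.

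Much of this stands. The omission is an inference from the criteria, and the all-randomised reading is possible. But the article does not state that reading, and its inclusion criteria, exclusion criteria and description of who is included all run against it. The point is not that a safety set is undefined; it is that the stated criteria exclude the patients the comparison is meant to address.

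Some stronger readings are tempting and not supported:

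- *That restriction to DCIS by itself biases the difference between arms.* Nothing here shows that. It changes the population and costs precision. The demonstrable direction comes from the VAE-only haematoma exclusion.
- *That the excluded patients are exactly those without DCIS, with no prospect of benefit.* High-grade, invasive and unoperated cases are excluded too, and the Discussion cites work on VAE for benign and high-risk lesions.
- *That the minimal-risk statement in the Conclusions would rest on this subset.* It is a prior statement about the design, not a result to be drawn from the comparison.
- *That this is critical to the trial.* Complications are outside the primary and secondary aims, and no power or margin depends on them.

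**Conclusion.** The concern holds as a conflict between the stated criteria and the purpose of the complication comparison, with moderate severity. Taken literally, the criteria leave out the patients whose exposure prompted the comparison, and they remove some haematomas from the VAE arm alone, which can only flatter VAE.

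The scale is illustrative. It rests on assumed yields, an assumed 5% complication rate and an unresolved reading of the 300. If the 300 are DCIS patients, the contrast between 7.2 and 4.9 points does not apply: the counted set already has 150 per arm, although still more exposed patients go uncounted. If the sponsor intends to compare all randomised patients, only the wording needs changing.

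**What to change.** In Exclusion criteria, and where the Discussion promises the comparison, state that:

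1. haematomas and peri-biopsy complications are compared in every randomised patient in whom the biopsy was started, by assigned arm, whatever the histology, whether or not surgery follows, and whether or not a haematoma stopped the second sequence;
2. the DCIS and surgery criteria apply to the efficacy endpoints only;
3. complication rates are also reported separately for patients without qualifying DCIS.

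It would help to say in the same place whether the 300 counts biopsied or DCIS patients.

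The cost is wording, plus keeping the Table 1 record for every patient biopsied. No added patients, visits or procedures are needed, and no clinical rule changes, only who is counted. The article does not state when consent is signed, so the sponsor should confirm that it covers keeping data on patients who later prove not to have DCIS. The downside is that the reported complication figures may be less favourable. The change is best made before records of excluded patients are discarded.
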